## Abstract

**Background:**

In the UK, children with high levels of hyperactivity, impulsivity and inattention referred to clinical services with possible attention-deficit/hyperactivity disorder (ADHD) often wait a long time for specialist diagnostic assessment. Parent training (PT) has the potential to support parents during this difficult period, especially regarding the management of challenging and disruptive behaviours that often accompany ADHD. However, traditional face-to-face PT is costly and difficult to organise in a timely way. We have created a low-cost, easily accessible PT programme delivered via a phone app, Structured E-Parenting Support (STEPS), to address this problem. The overall OPTIMA programme will evaluate the efficacy and cost-effectiveness of STEPS as a way of helping parents manage their children behaviour while on the waitlist. To ensure the timely and efficient evaluation of STEPS in OPTIMA, we have worked with children’s health services to implement a remote strategy for recruitment, screening and assessment of recently referred families. Part of this strategy is incorporated into routine clinical practice and part is OPTIMA specific. Here, we present the protocol for Phase 1 of OPTIMA—a study of the feasibility of this remote strategy, as a basis for a large-scale STEPS randomised controlled trial (RCT).

**Methods:**

This is a single arm observational feasibility study. Participants will be parents of up to 100 children aged 5-11 years with high levels of hyperactivity/impulsivity, inattention and challenging behaviour who are waiting for assessment in one of five UK child and adolescent mental health or behavioural services. Recruitment, consenting and data collection will occur remotely. The primary outcome will be the rate at which the families, who meet inclusion criteria, agree in principle to take part in a full STEPS RCT. Secondary outcomes include acceptability of remote consenting and online data collection procedures; the feasibility of collecting teacher data remotely within the required timeframe, and technical difficulties with completing online questionnaires. All parents in the study will receive access to STEPS.

**Discussion:**

Establishing the feasibility of our remote recruitment, consenting and assessment strategy is a pre-requisite for the full trial of OPTIMA. It can also provide a model for future trials conducted remotely.

**Supplementary Information:**

The online version contains supplementary material available at 10.1186/s40814-021-00959-0.

## Background

Attention-deficit/hyperactivity disorder (ADHD) is a debilitating neurodevelopmental condition that is characterised by symptoms of inattention and/or impulsivity and hyperactivity and affects about 4% of UK children [1]. ADHD is associated with substantial impairment for the child across multiple life domains [2–5]. It also negatively affects carers’ mental health and family wellbeing [6]. Up to 90% of children with an ADHD diagnosis also display a broader pattern of behaviour problems (e.g., oppositional, disruptive, defiant and challenging behaviours) and often meet the criteria for oppositional defiant disorder (ODD) [7]. This exacerbates the levels of impairment experienced by children with ADHD [8] and presents a major challenge to parents, increasing levels of parenting stress [9] and mental health problems [10]. These challenging behaviours contribute to coercive child-parent relationships that can deteriorate over time [11]. It is the escalation of these challenging behaviours to crisis levels that often leads parents with children, who have high levels of hyperactivity/impulsivity and inattention, to first seek professional help [12]. For many parents, finding a way to manage their child’s disruptive and defiant behaviour is likely to be the most urgent treatment priority at the time of their referral to child and adolescent mental health services (CAMHS).

Consistent with this, the National Institute for Health and Care Excellence (NICE) recommends that parent training should be made available to families whose children are referred with hyperactivity/impulsivity and inattention, especially where these are accompanied by challenging and disruptive behaviour, soon after their referral is made, allowing them to start addressing their children’s behavioural difficulties early on [1]. Parent training is an existing evidence-based intervention for disruptive and defiant behaviour displayed by children with ADHD, which helps parents to find more effective ways to manage their children’s behaviour [13].

However, currently, the means to deliver this intervention in a timely manner soon after a referral is lacking. This is because parent training is traditionally delivered face-to-face either in small groups or on a one-to-one basis and is costly to provide and time-consuming to organise [14]. Because of this, typically, parent training is only offered after a full-clinical assessment has been made and an ADHD diagnosis is given. The long waiting lists that currently exist for CAMHS mean that parents can be left without support and guidance for extended periods while waiting for the assessment. For example, the Children’s Commissioner Lightening Report in 2016 found up to 200 days delay to initial assessment [15]. Having to wait for parent training carries a substantial risk of further deterioration of the parent-child relationship and escalation of their child’s problems—with concomitant probable effects on parent and family wellbeing that this implies.

To address this problem, we have developed a new digital way to deliver support to parents to help them manage the challenging behaviour of their children referred with hyperactivity/impulsivity and inattention—Structured E-Parenting Support (STEPS). STEPS is a low-cost, easy and quick to access parenting support intervention delivered as a mobile phone application (app). It is designed to provide established evidence-based advice and support for parents, whose children display hyperactivity/impulsivity, inattention, to help them better manage their children’s co-occurring disruptive and oppositional behaviours. Inspired by the New Forest Parenting Programme [16], a face-to-face parent training programme, its content has been shaped by the latest research about parenting and child behaviour [13, 14, 17] as well as many years of clinical experience and the views of families of children with ADHD-type problems. Key treatment objectives include: (1) increasing parents’ knowledge of why some children’s behaviour is more difficult to manage than others, (2) building their child’s confidence, (3) facilitating effective communication patterns and (4) giving parents strategies to facilitate more effective management of their child’s challenging behaviour. The content is delivered in eight steps, each following a standard structure with common audio-visual and graphic elements describing and illustrating recommended parenting practices and skills. For a more detailed overview of STEPS, see Supplementary Documents (1. Structured E-Parenting Support).

## The present study

We have been funded by the UK National Institute for Health Research (NIHR) to evaluate STEPS as a way of delivering parent training to families of children who have been referred to children’s services and are waiting for specialist assessment and treatment. The programme of research is called *On-Line Parent Training for the Initial Management of ADHD referrals* (OPTIMA [RP-PG-0618-20003]). Its main component is a large multi-centre randomised control trial (RCT) comparing STEPS with waiting as usual (STEPS RCT). However, before we can proceed with this full RCT, we need to establish that we can recruit sufficient new CAMHS and early behavioural services referrals with hyperactivity/impulsivity, inattention and challenging behaviour to provide adequate statistical power for this evaluation. To this end, we have worked with children’s services to implement a remote digital strategy for recruitment, screening and assessment of recently referred families—part of which is incorporated into routine clinical practice and part of which is OPTIMA specific. Using remote digital methods ensures rapid and systematic screening of ADHD and ODD symptoms in children accepted by children’s health services from different referral sources and provide parents with access to support as soon as possible, in the form of STEPS. This strategy also reduces administrative burden and the gatekeeping function of local clinicians in a way that gives parents greater autonomy in decisions to participate in research. The aim of Phase 1 of the OPTIMA programme is to assess the feasibility of this remote strategy as a basis for a full-scale RCT.

## Methods

### Study objective

The primary objective of the study is to test whether we can use our remote recruitment, consenting and assessment strategy to recruit recent referrals to children’s services (CAMHS and early behavioural support services) at a sufficient monthly rate to provide statistical power for our planned STEPS RCT.

Secondary objectives include establishing the usability and acceptability of our remote recruitment, consenting and assessment strategy including the online outcome and adverse events collection procedure. We will also assess the feasibility of collecting teacher data remotely within the required timeframe and capture technical difficulties completing online questionnaires.

This study will not pilot or test the feasibility of the STEPS app as a form of a parent training intervention.

### Design

This will be a single-arm observational feasibility study.

### Setting

The study will be conducted remotely (using phone calls and digital methods), with researchers based in three trial centres: London, Southampton and Nottingham (UK). Recruitment will take place across five sites: South London and Maudsley NHS Trust (SLaM), Solent NHS Trust, North East London NHS Foundation Trust (NELFT), Black Country Healthcare NHS Foundation Trust and Nottingham City Council. These five sites have been selected as they have (i) an early triage system through which referrals are placed on a child and adolescent mental health services (CAMHS) pathway, or (ii) use a digital portal (myHealthE [18] or Interactive CAMHS Assessment Network) to screen for hyperactivity/impulsivity, inattention and challenging behaviour using the Strengths and Difficulties Questionnaire [19] and to establish consent for contact (C4C).

### Participants

Participants in the study will be parents of children aged 5 to 11 years that passed the initial triage and have been accepted onto the services’ assessment waiting list and the children’s teachers.

#### Inclusion criteria

Parent of a new referral. A ‘new referral’ is defined as a child who has been on a waitlist for no longer than six calendar months.A routine positive screen for child’s hyperactivity/impulsivity, inattention and challenging behaviour using the SDQ (hyperactivity/inattentive subscale score ≥ 8 and conduct problems subscales score ≥ 4). These scores represent the “high” and “very high” problem groups according to the four-band classification of the SDQ cut off scores (top 10% of the population) [20].

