### Sample size

The primary aim of the feasibility study is to establish that we can recruit enough parents of new referrals for the STEPS RCT using our remote strategy incorporating existing routine CAMHS triage and clinical screening elements using MHE, ICAN or telephone-based methods across the five recruitment sites (Fig. 2). Based on the power calculations for the larger planned RCT of STEPS, we need to recruit 13 participants a month (352 families over 27 months). We will base our assessment of whether this is possible on the primary feasibility outcome described above, the rate per month of participants who answer the STEPS RCT feasibility question in the affirmative. Because we assume it is more likely that people would agree in principle to take part in STEPS RCT during the feasibility study than would actually consent to the real trial, we have adopted a conservative requirement in this feasibility of 18 (rather than 13) parents a month as our aim in this feasibility study and our stop/go criterion for the larger trial.

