**Fig. 2 Fig2:**
[figure not shown]
Estimated monthly referral flow

The numbers of potential participants at each stage of the selection process during each month of the feasibility study is shown in Fig. 2. Based on audit and best information across our trial sites, we estimate that each month, parents of 200 newly referred children (of roughly 750 referrals across the 5 sites) will be eligible to take part in the feasibility study. We estimate that 50 parents would consent to the feasibility study and of these roughly 25 will give a positive response to the feasibility question, which is above the number required.

We will test this by recruiting 25 study eligible parents (half of the number available) each month (100 over 4 months). Our projections will be supported if 12 or so of these parents answer the feasibility question positively. This number will also give us a good sample in which to assess our other feasibility measures.

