### Ethics

The application for ethical approval for the study was submitted to the London-Riverside Research Ethics Committee (REC) and received a favourable opinion on further information on 17 November 2020, REC reference number: 20/LO/1173.

To allow maximum flexibility in terms of recruitment, a substantial amendment to the ethical application was submitted to the REC in March 2021. This amendment introduced two additional methods of participant identification (Method 2: ICAN and Method 3: a manual review of referral lists). This amendment was approved in April 2021. The REC was notified of two further non-substantial amendments, which did not require study-wide review, one in May 2021 and the second one in June 2021. The current manuscript is based on protocol version 5.0 dated 10 June 2021.

Recruitment for the study commenced in April 2021 and will continue until the end of July 2021.

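### A six-month look-back in a four-month study counts already-waiting families with new referrals, so the monthly rate may overstate what the RCT can sustain

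*Protocol article*

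**What the plan says.** Under Inclusion criteria, a new referral is "defined as a child who has been on a waitlist for no longer than six calendar months". No text restricts entry to children referred after a site opens. The Ethics section gives the recruitment period: "Recruitment for the study commenced in April 2021 and will continue until the end of July 2021". That is four months, shorter than the look-back.

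The planning figures in the Sample size section are monthly flows: "each month, parents of 200 newly referred children (of roughly 750 referrals across the 5 sites) will be eligible to take part". The section continues: "We estimate that 50 parents would consent to the feasibility study and of these roughly 25 will give a positive response". The study itself plans to take 25 parents a month, 100 in all, which it describes as half of what is available. It regards the projections as supported if about 12 of each 25 answer yes.

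For the RCT, "we need to recruit 13 participants a month (352 families over 27 months"). The stop/go criterion is "a conservative requirement in this feasibility of 18 (rather than 13) parents a month", and the only reason given for the margin is over-agreement: "Because we assume it is more likely that people would agree in principle to take part in STEPS RCT" than would consent to the real trial.

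The Outcomes and Statistical analysis sections define the primary outcome as a count of positive answers per month. Neither separates children already waiting at opening from children referred afterwards.

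**The concern.** Eligibility is defined on a stock (everyone who has waited up to six months), while the projection and the RCT requirement are flows (new referrals per month). On its first day a site can hold up to six months of earlier referrals that already meet the definition. Spread over four months, that one-off stock could make up much of the count; over 27 months the same stock would matter little.

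The rate decides whether a 352-family RCT goes ahead. If part of it comes from families who can be recruited only once, the steering committee could read a temporary supply as a sustainable one. As the outcome is defined, places filled from stock and places filled from flow look the same.

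**Working it through.** **Inputs from the protocol article**
- Look-back: 6 months (Inclusion criteria).
- Feasibility recruitment: 4 months (Ethics).
- RCT need: 352 families in 27 months; stop/go: 18 a month (Sample size).
- Monthly projection: 200 eligible, 50 consents, 25 positive answers; planned intake 25 a month, 100 in total (Sample size).

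**Assumptions, not in the document**
- b, the usable backlog at opening expressed in months of flow, is not given. Range used: 0 to 6.
- Flow is constant, and reachable backlog families consent and agree at the same rates as new ones.
- The RCT's look-back and opening stock are not stated. Both cases are shown: no RCT backlog, and the same b.

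**1. The plan's own figures reproduce.** 352/27 = 13.04 a month, and 13 × 27 = 351. Consent is 50/200 = 25%; agreement is 25/50 = 50%; 25 × 4 = 100; 25 × 0.5 = 12.5, matching the plan's figure of about 12.

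**2. Inflation with uncapped intake.** Over T months the pool is T + b months of flow, so the average monthly rate is inflated by (T + b)/T. If 18 a month is observed, the underlying flow is 18 × 4/(4 + b).

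| b (months) | Feasibility (4+b)/4 | RCT (27+b)/27 | Ratio | Flow behind an observed 18 | 27-month total, no RCT backlog | 27-month total, same b |
|---|---|---|---|---|---|---|
| 0 | 1.00 | 1.00 | 1.00 | 18.0 | 486 | 486 |
| 1 | 1.25 | 1.04 | 1.21 | 14.4 | 389 | 403 |
| 2 | 1.50 | 1.07 | 1.40 | 12.0 | 324 | 348 |
| 3 | 1.75 | 1.11 | 1.58 | 10.3 | 278 | 309 |
| 6 | 2.50 | 1.22 | 2.05 | 7.2 | 194 | 238 |

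The need is 352.

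**3. Backlog that uses up the margin.** The margin is 18/13.04 = 1.38.
- RCT without backlog: 18 × 4/(4 + b) = 352/27, so b = 4 × (1.381 − 1) = 1.52 months.
- RCT with the same backlog: 72 × (27 + b) = 352 × (4 + b), so 536 = 280b and b = 1.91 months.

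At either point nothing is left for over-agreement, which is what the margin was set for.

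**4. The planned intake of 25 a month.** With c consents a month from flow and B from backlog, all places are filled when 4c + B reaches 100. Take c = 10 and a full six-month backlog at that flow, B = 6 × 10 = 60. Then 40 + 60 = 100. At 50% agreement the study records 50 positive answers, 50/4 = 12.5 a month, which the Sample size section would read as supporting its projections. Flow alone sustains 10 × 0.5 = 5 a month.

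Conversely, if flow yields 25 or more consents a month, backlog does not change the count. At the projected 50, the capped 12.5 understates the flow of 25 positive answers.

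**The case against.** The best case against the point is the intake limit. Only 25 parents a month are to be taken and the projected flow supplies 50 consents, so on the plan's own figures no backlog is needed. This stands as a limit: backlog affects the count only if flow falls below 25 consents a month. It does not remove the point, because the flow of 50 is the projection that the study is there to test.

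The document also suggests that much of the backlog is out of reach. A child needs a positive SDQ screen, and the routes depend on consent for contact or on a clinician raising the study. The Discussion says that waiting families have little clinician contact and are usually asked about research contact only at assessment. Under Method 1, staff load new referrals into the portal. The delay of up to 200 days in the Background is an upper figure from a 2016 report. So b is probably well below 6, but it is not zero by design: Method 3 works from current referrals and may be used at any site, even alone, and the listed criteria for the Method 1 eligibility flag include no referral date.

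There may also be a pull downwards. Methods 2 and 3 were approved only in April 2021, and their start-up could depress a four-month average. That is a further reason not to assert a net upward bias.

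Finally, an analysis plan was being developed and is not shown, and the independent steering committee includes a statistician. Either could deal with the source of recruits. But the look-back, the outcome and the threshold are all fixed in this article.

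**Conclusion.** The point holds as a possibility of unknown size. The observed monthly rate may overstate sustainable recruitment by a factor between 1.0 (no usable backlog) and 2.5 (full six-month backlog, uncapped intake), or at most about 2.05 relative to a 27-month RCT with the same window and backlog. Under the planned intake, the realistic harm is that backlog hides a flow of fewer than 25 consents a month. The 18-versus-13 margin would absorb only about 1.5 to 1.9 months of usable backlog.

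Two stronger readings are tempting and are not supported. One is that the rate does overstate: the document gives neither the backlog nor the RCT's window, and at b = 0 there is no overstatement. The other is that a go could rest on backlog alone, because an opening stock of 6 × 200 = 1,200 families at 25% consent gives 300 consenters, three times the study. Intake is planned at 100, so that count could not be observed. At 50% agreement, 25 a month give 12.5 positive answers; reaching 18 would need 18/25 = 72%. The stock of 1,200 also presumes the very flow of 200 a month at which no backlog is needed.

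**What to change.** Use each child's waitlist entry date, which is already needed to apply the six-month rule, and:

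- report the monthly rate of positive answers separately for children referred before and after their site opened;
- base the stop/go comparison with 18 on the post-opening rate, or on yield (positive answers divided by all eligible referrals reviewed, backlog included in the denominator) multiplied by new eligible referrals per month;
- show the all-comers rate as an upper bound only.

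The cost is some analysis wording and one derived variable. No new data collection is needed, so the change remains possible although Study status reports recruitment as complete. The downside is that the rate may look less favourable. The post-opening rate alone is also slightly conservative because identification lags referral, and places given to already-waiting families under a limited intake displace new ones. Both are reasons to prefer the yield version, or to present the two together.

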#### Exclusion criteria

Parent lacks access to a suitable electronic device: a smartphone with operating system OS 4.1 and later (Android devices) or iOS 9.0 (Apple devices).Child is living under Local Authority care.Parent has an insufficient level of English language.

Foster parents of children living under local authority care have been excluded, as many foster placements are shorter than 12 months, which will be the duration of the follow-up in the RCT of STEPS.

There will be no inclusion/exclusion for teachers, but researchers will need to obtain parents’ permission for contacting teachers.

### Intervention

Although this is not a study of the STEPS app, we provide a brief overview of the app for information (more details can be found in Supplementary Documents: 1. Structured E-Parenting Support). In STEPS, parents will be able to move through the content (steps) at their own pace and at any time of day. The order of the steps is fixed, but there will be a degree of choice within each step. The content will be delivered mainly using short videos and audio clips.

The STEPS app has one preparatory module, “Introduction”, followed by eight separate intervention modules (steps). How long STEPS takes to complete will depend on the pace and frequency of usage. However, each of the eight steps is designed to take about 20 min if completed in one go. Parents will be able to use STEPS for 12 weeks from the time they download the app. The access to the app will be blocked 12 weeks after download, as the team will not be able to monitor the participants after that time. There will be no restrictions on concomitant care or interventions.

